## Abstract

**Background:**

Endovascular procedures using a mobile C-arm are commonly performed in patients with peripheral artery disease. During these procedures, digital subtraction angiography (DSA) requires intra-arterial administration of contrast agent and exposes both patients and staff to radiation from the C-arm. The Vascular Navigation PAD system (Brainlab, Germany) may reduce the number of DSAs performed and thereby decrease both contrast agent use and radiation exposure. The objective of this study is to evaluate the safety and clinical performance of the Vascular Navigation PAD system compared with standard care in endovascular PAD treatment. The primary aim is to determine whether the device reduces the volume of contrast agent used during lower-extremity procedures. Secondary objectives include assessing patient and physician radiation exposure, patient air kerma, and the device’s ability to support accurate endovascular navigation.

**Methods:**

This is a multicenter, prospective, randomized confirmatory trial comparing navigation-assisted procedures with conventional procedures without navigation assistance. Patients allocated to the intervention group will undergo treatment using Vascular Navigation PAD in addition to a mobile C-arm. A total of 160 patients will be randomized in a 1:1 ratio, with 40 patients per group enrolled at each of the two participating hospitals. The primary endpoint is contrast agent volume. Secondary endpoints include patient radiation exposure, physician radiation exposure, fluoroscopy time, and the number of DSAs performed per intervention.

**Discussion:**

This study will evaluate whether the Vascular Navigation PAD system can reduce the number of DSAs in endovascular treatment. A reduction in DSAs may lead to lower contrast agent use and reduced radiation exposure for both patients and staff.

**Trial registration:**

The clinical trial is registered at the German Clinical Trials Register (ID: DRKS00035267). Registered on 10.Jan.2025.

## Introduction

### Background and rational {6a}

Peripheral artery disease (PAD) is becoming increasingly common [1]. It is characterized by stenoses or occlusions of the arteries, predominantly in the lower extremities, leading to impaired distal blood flow. Clinical manifestations range from intermittent claudication (IC) to critical limb ischemia (CLI) and arterial ulceration [2]. In patients with symptomatic PAD, revascularization may be considered, and endovascular procedures have become a central treatment option [3].

Endovascular procedures are often performed using a mobile C-arm for fluoroscopic and angiographic imaging [4]. Contemporary mobile C-arms can generate angiographic roadmaps after a digital subtraction angiography (DSA) provided that neither the patient nor the C-arm moves. These roadmaps provide a detailed representation of the patient’s vascular system, assisting in navigating through the arteries to reach the affected areas. However, previously acquired DSAs cannot generally be reused after repositioning. As a result, repeated angiography is often required, which increases radiation exposure and contrast agent administration. DSAs are known to be the primary radiation source during these procedures and contribute to the likelihood of stochastic radiation effects [5]. Because contrast agents are administered intra-arterially and may be nephrotoxic, minimizing their use is clinically relevant, particularly in a patient population with frequent comorbidities such as diabetes and reduced renal function [6].

The Vascular Navigation PAD system (Brainlab, Munich, Germany) provides image guidance during endovascular PAD procedures of the lower limbs, including the iliac arteries. It receives image data from the angiographic system, processes selected images, and constructs a vessel tree from multiple angiographic images. This enables continuous localization of endovascular devices relative to vascular anatomy by overlaying the vessel tree on live fluoroscopy. If a matching image pair is available, a repeat DSA may not be necessary after repositioning the C-arm. A CE certificate was issued in June 2024; the FDA approval is pending.

The primary aim of this study is to determine whether the investigational device reduces contrast agent volume during endovascular procedures of the lower extremities. Secondary aims are to measure radiation dose to patients and staff and to assess the device’s ability to support navigation of endovascular devices to predefined targets in PAD procedures.

This is the first clinical study of the new Vascular Navigation PAD. Retrospective studies with the EndoNaut 2D fusion imaging system (Therenva, Rennes, France), a comparable device, showed a reduction in contrast agent use [7, 8]. A randomized prospective study is therefore needed to evaluate these findings in a controlled setting.

### Objectives {7}

The study compares the investigational device with current standard care in endovascular treatment of PAD. It will evaluate whether use of the Vascular Navigation PAD system reduces the volume of contrast agent required during lower-extremity endovascular procedures. Because this is a post-market clinical follow-up study, both clinical effectiveness and safety are part of the evaluation.

#### Primary objective

The primary objective is to determine the ability of the Vascular Navigation PAD to reduce the volume of administered contrast agent compared to procedures performed without the device.

#### Secondary objectives

The secondary objectives of this study are to evaluate the following:Radiation dose received by patients during surgeries with and without the deviceRadiation dose received by the physicians during surgeries with and without the devicePatient air kerma received during surgeries with and without the deviceQualitative assessment of the device ability to enable navigation of endovascular devices to defined targets in PAD procedures

### Trial design {8}

This study is a multicenter, two-arm, prospective, confirmatory randomized superiority trial comparing a study group (navigation assistance) with a control group (procedure without navigation assistance). Patients with a clinical diagnosis of PAD who are eligible for endovascular treatment will be randomized to standard treatment or treatment with the Vascular Navigation PAD system in a 1:1 ratio.

## Methods: participants, interventions, and outcomes

### Study setting {9}

The study will be conducted in the tertiary University hospital Augsburg, Germany and the tertiary University hospital RWTH Aachen, Germany. A total of 160 patients will be recruited with equal allocation across sites and study groups.

The study population comprises adult patients with PAD and stenotic lesions in the lower extremities who are candidates for endovascular treatment.

### Eligibility criteria {10}

Below are the inclusion and exclusion criteria of this trial:

#### Inclusion criteria

Subject has been diagnosed with peripheral arterial disease of the lower limbs or iliac arteries with Rutherford category 2–6Subject is eligible for endovascular surgerySubject provides written informed consentSubject is ≥18 years

#### Exclusion criteria

Subjects will be excluded from participating in this clinical investigation if one or more of the following exclusion criteria are met:Subject requires bypass surgery or other conventional surgery revascularization for a target lesionSubject has a known contrast agent allergySubject is pregnant or nursingSubject is unable to consent

#### Performing surgeons

The interventions will be performed by a specialist in vascular surgery at the two participating hospitals.

### Who will take informed consent? {26a}

The investigator will inform potential patients both orally and in writing about the study procedures, as well as their responsibilities and rights while participating. The investigator will address all questions posed by the potential subjects. Each potential patient will sign and date two copies of the informed consent form at least 24 h before surgery. The forms will also be signed and dated by the investigator as a witness to the patient’s signature. The patient will receive one copy of the patient information, while the investigator will retain the other signed informed consent form.

### Additional consent provisions for collection and use of participant data and biological specimens {26b}

Additionally, participants of this trial can give informed consent for collecting preoperative CT-scans, but it is not mandatory for participating. The collected CT-scans are used for later comparison with intraoperative imaging. If the participants do not consent to collecting the CT-scans, the preoperative data will be used and stored in accordance with the local regulations of the treating hospital.

No biological specimens will be collected or stored for this trial.

## Interventions

### Explanation for the choice of comparators {6b}

The control group will undergo endovascular revascularization using X-ray fluoroscopy with a mobile C-arm, including roadmapping when available. This reflects standard care in German hospitals for PAD interventions, as hybrid operating rooms are not widely available. Mobile flat-panel C-arm systems will be used in both groups.

### Intervention description {11a}

No specific pre-planning procedures involving patient data are required. Patients will receive treatment according to standard clinical procedures using a mobile flat-panel C-arm. The treating physician will determine the procedural steps, including stenting if indicated. The protocol therefore focuses on the study-specific elements rather than providing a fully detailed description of routine clinical care.

Any steps that deviate from the standard of care are highlighted in bold. The subsequent section delineates, in broad terms, the intraoperative workflow with the trial device during a PAD procedure:The mobile flat-panel system will be started and connected via HDMI with the Brainlab hardware running Vascular Navigation PAD.The patient will be transported to the OR. Patient is under local, regional, or general anesthesia.A vascular sheath will be placed at the surgeon’s discretion.The surgeon will create one or more roadmaps according to the device functionality principle, by capturing DSAs and fluoroscopic images within the Vascular Navigation PAD. This capturing process is within the intended use of the investigational device, but additional to the standard of care at the study site.

Note: Image acquisition is done using a flat-panel angiographic imaging device. Acquisition of those image types is standard protocol during endovascular procedures and therefore does not add additional radiation exposure to the clinical procedure.Optional: The surgeon may mark areas of suspected lesions within the Vascular Navigation PAD.The captured images will be stitched together to generate a vessel tree. Image recognition will suggest anatomical overlap, which the surgeon may manually adjust and must confirm.The created (continuous) roadmap(s) will be used to support the navigation of endovascular tools to one or more lesions. The principle of single-image roadmaps is standard of care.The surgeon will then treat those lesions at their discretion and continue with the procedure as intended.The vascular access will be closed as usual (end of clinical procedure).

Post-operative:All image and video data in relation to the procedure (including preoperative imaging data) will be exported and uploaded to a secure platform.A CRF will be completed for each enrolled patient, and no additional diagnostic tests will be performed as part of the study.

### Criteria for discontinuing or modifying allocated interventions {11b}

Cross-over to Vascular Navigation PAD from state-of-the-art or vice versa is not according to protocol. A change from device group to the standard of care may at the discretion of the operating surgeon, and this information must be captured in the case report form. Reasons for the change would be the surgeon believing that the roadmap created by the Vascular Navigation PAD does not correspond to the actual vascular system.

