### Strategies to improve adherence to interventions {11c}

Reasons for non-compliance could include Vascular Navigation PAD failure, surgeon error, failure to communicate correct randomization allocation to the surgeon and OR personnel, and cross-over. The patient could impact compliance if they express a wish to withdraw between randomization and surgical procedure or in the event of death.

To improve adherence, treating surgeons and OR personnel receive annual training in the navigation system PAD in accordance with the German Medical Devices Act. The study documentation, including the randomization information, is brought to the operating room with the patient and reviewed by the surgeon before the procedure begins.

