### Sample size {14}

It is the aim of this study to determine the investigational device’s ability to reduce the nephrotoxic contrast agent volume required during endovascular procedures of the lower extremities. Existing clinical literature suggests a potential reduction of 30% in the volume of contrast agent when comparing procedures with navigation support to those without it [7, 9]. Additionally, information on usually needed contrast agent during procedures without navigation support is provided by a systematic review [9]. Reported values are as follows:Navigation-supported group = 34.7 ± 13.8 mLNon-navigated group (control):◦ Group 1 = 51.3 ± 26.7 mL [7])◦ Group 2 = 88.31 ± 55.35 mL (systematic review, [10])◦ Group 3 = 81.14 ± 58.68 mL (systematic review, [10])

Based on this clinical literature, the expected mean contrast volume was assumed to be 88.16 mL in the control group and 34.7 mL in the navigation-assisted group, corresponding to an anticipated absolute reduction of 53.46 mL. For sample size planning, a superiority margin of 30% of the control-group mean was prespecified, corresponding to 26.45 mL, which was used as the clinical threshold for superiority and not as the expected treatment effect. Assuming a common standard deviation of 55.27 mL, a two-sided significance level of 0.05, and a power of 90%, the required sample size was calculated for a two-group superiority design with a continuous endpoint.

After allowing for a dropout rate of 10%, 80 patients per group were planned.

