## Statistical methods

### Statistical methods for primary and secondary outcomes {20a}

The primary and secondary endpoints will be summarized as mean ± standard deviation or median, as appropriate. Because contrast agent volume and radiation dose are continuous variables and each participant contributes one observation, group comparisons will be performed using an unpaired two-sample *t*-test if the data are approximately normally distributed. The primary analysis will be conducted according to the intention-to-treat principle.

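### Against the 26.45 mL margin, the planned 80 per group leave no room for device-arm procedures changed to standard care, although intention-to-treat keeps those patients in the device arm

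*Protocol article*

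**What the plan says.** All references are to the protocol article.

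- **Criteria for discontinuing or modifying allocated interventions {11b}.** One sentence calls cross-over in either direction off-protocol. The next reads: "A change from device group to the standard of care may at the discretion of the operating surgeon". The reason given is a roadmap that the surgeon believes does not match the vessels, and the change must be recorded in the case report form (CRF).
- **Strategies to improve adherence {11c}.** Further routes to an un-navigated device-arm procedure are listed: "Reasons for non-compliance could include Vascular Navigation PAD failure, surgeon error, failure to communicate correct randomization allocation", and cross-over.
- **Statistical methods {20a}.** "The primary analysis will be conducted according to the intention-to-treat principle". The test is an unpaired two-sample t-test if the data are approximately normal. The margin is not mentioned.
- **Sample size {14}.** "the expected mean contrast volume was assumed to be 88.16 mL in the control group and 34.7 mL in the navigation-assisted group". The planning effect is the difference of these two means, 53.46 mL. Then "a superiority margin of 30% of the control-group mean was prespecified, corresponding to 26.45 mL", described as the threshold for superiority and not the expected effect. The common SD is 55.27 mL, with "a two-sided significance level of 0.05, and a power of 90" per cent. The only allowance is for dropout: "After allowing for a dropout rate of 10%, 80 patients per group were planned".

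**The concern.** A dropout allowance replaces lost observations. It does nothing for patients who stay in the analysis but did not have the navigated procedure. Under intention-to-treat such patients pull the device-arm mean towards the control mean, so the expected difference is smaller than the one used for planning.

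The margin magnifies this. The working difference is not 53.46 mL but its excess over 26.45 mL, and all the dilution falls on that excess. The Introduction calls this the first clinical study of the device, so the document gives no support for assuming that no procedure is changed. At stake is the reading of a negative primary result: it could reflect abandoned navigation and be taken as evidence that the device does not work.

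**Working it through.** **Inputs from {14}.** Means 88.16 and 34.7 mL; common SD 55.27 mL; margin 26.45 mL; 80 per group; 10% dropout.

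- Expected effect: 88.16 − 34.7 = 53.46 mL.
- Excess over the margin: 53.46 − 26.45 = 27.01 mL.
- Evaluable per group: 80 × 0.90 = 72.

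**Assumptions, not in the documents.** A share c of device-arm procedures is changed, shown for 0 to 20%. Changed cases have the control mean. The SD is unchanged.

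**Step 1: reproduce the plan's figure** (normal approximation).
n per group = 2 × 55.27² × (z_α + 1.282)² / 27.01²

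- Two-sided 0.05 (z_α = 1.960): n = 88; 88 / 0.90 gives 98 per group.
- One-sided 0.05 (z_α = 1.645): n = 72; 72 / 0.90 gives 80 per group.

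Of the variants tried, only the one-sided test against the margin gives 80. Testing the full 53.46 mL against zero, two-sided, would need only 23 per group (26 after dropout). So the planned 80 is a margin-based number, but not at the stated sidedness.

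**Step 2: dilution.**
Intention-to-treat effect = 53.46 × (1 − c). Each 10% changed removes 0.10 × 53.46 = 5.35 mL, and 5.35 / 27.01 is about one fifth of the excess.

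**Step 3: power at 72 evaluable per group.**
Standard error = 55.27 × √(2/72) = 9.21 mL.
Power = Φ((53.46 × (1 − c) − 26.45) / 9.21 − z_α)

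| c | Effect (mL) | Excess over margin (mL) | Power, two-sided 0.05 | Power, one-sided 0.05 |
|---|---|---|---|---|
| 0% | 53.46 | 27.01 | 83.5% | 90.1% |
| 5% | 50.79 | 24.34 | 75.2% | 84.1% |
| 10% | 48.11 | 21.66 | 65.2% | 76.0% |
| 20% | 42.77 | 16.32 | 42.5% | 55.0% |

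Example, c = 10%, two-sided: 21.66 / 9.21 − 1.960 = 0.39, and Φ(0.39) is about 65%.

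In the one-sided variant 90% is kept only up to c of about 0.1%. Adding the extra variance from mixing two means in the device arm lowers the figures a little further (c = 10%, two-sided: 63.5%).

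**Step 4: the same with a null of zero** (two-sided, 72 per group).
Power = Φ(53.46 × (1 − c) / 9.21 − 1.960): above 99.9% at c = 0 and 10%, 99.6% at 20%. For 90% an effect of (1.960 + 1.282) × 9.21 = 29.86 mL is needed, so c may reach 1 − 29.86 / 53.46, about 44%.

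**The case against.** Four arguments limit the point.

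1. **The null.** {20a} names an ordinary t-test without a margin. Read as a test of zero difference, dilution is harmless at every rate tabulated. This stands, and the conclusion is therefore conditional. It does not remove the point, because the 80 per group comes from the margin calculation in {14}.
2. **The SD.** {14} cites 34.7 ± 13.8 mL for the navigated group, so a common 55.27 mL is conservative for that arm. With SD 13.8 mL for navigated cases, control mean and SD for changed cases and the mixture variance included, two-sided power against the margin at 72 per group is about 98% at c = 0, 94% at 5%, 91% at 7% and 85% at 10%. Some room for changes would then exist. But the plan states the common SD, and its 90% is a claim under that SD.
3. **The rate and the changed cases.** No rate of change is given, and training and a pre-procedure allocation check in {11c} should limit some causes. The source of the 34.7 mL may already include converted procedures, in which case deducting c counts them twice. A changed patient may use less contrast than a control, or more because roadmap angiograms were already made. All this affects the size, not the absence of an allowance.
4. **The estimand.** Intention-to-treat answers a pragmatic question, and the dilution is part of that answer. Agreed, and the planning effect should then be on the same scale. Supplementary analyses can be left to an analysis plan that is not shown, and their absence is no fault here.

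**Conclusion.** The point holds in conditional form. If superiority is tested against the 26.45 mL margin with SD 55.27 mL and changed cases at the control mean, the planned size has no allowance for changed procedures. Ten per cent changed costs 18 percentage points of power at two-sided 0.05 (83.5 to 65.2%) and 14 at one-sided 0.05 (90.1 to 76.0%).

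Two stronger readings are tempting and are not supported. A reader might infer that 90% is secured as long as no procedure is changed. At the stated two-sided 0.05 it is 83.5% even then, so part of the shortfall is a mismatch of sidedness and not dilution. A reader might also infer that the trial is underpowered whatever the test. Against zero it is not, up to about 44% changed, and with the cited navigated SD the loss against the margin is smaller. Sections {14} and {20a} do not settle which null applies, and that has to be resolved before any single power figure can be relied on.

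**What to change.** - In {14}, state the null hypothesis (margin or zero) and the sidedness, and make {20a} say the same.
- In {14}, express the planning effect as 53.46 × (1 − c) mL, with c the assumed share of device-arm procedures changed to standard care. Replace the single 90% with the power of the planned 80 per group (72 evaluable) for c = 0, 5, 10 and 20%. Keep the sample size.
- Report the observed share changed beside the primary result. A supplementary complier-average estimate would help separate dilution from lack of effect, but is optional.
- Reconcile the two sentences on cross-over in {11b}, so that it is clear whether a change to standard care counts as a protocol deviation. Which clinical rule applies is for the sponsor and investigators.

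The cost is a few sentences and a small table. No patients are added, and the share changed is already captured in the CRF. If the margin is the null, the stated power becomes less favourable.

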### Strategies to improve adherence to interventions {11c}

Reasons for non-compliance could include Vascular Navigation PAD failure, surgeon error, failure to communicate correct randomization allocation to the surgeon and OR personnel, and cross-over. The patient could impact compliance if they express a wish to withdraw between randomization and surgical procedure or in the event of death.

To improve adherence, treating surgeons and OR personnel receive annual training in the navigation system PAD in accordance with the German Medical Devices Act. The study documentation, including the randomization information, is brought to the operating room with the patient and reviewed by the surgeon before the procedure begins.

